## Abstract

**Background:**

There are evidence-based interventions for depression that include different components. However, the efficacy of their therapeutic components is unknown. Another important issue related to depression interventions is that, up to now, their therapeutic components have only focused on reducing negative symptoms rather than on improving positive affect and well-being. Because the low levels of positive affect are more strongly linked to depression than to other emotional disorders, it is important to include this variable as an important treatment target. Positive psychotherapeutic strategies (PPs) could help in this issue. The results obtained so far are consistent and promising, showing that Internet-based interventions are effective in treating depression. However, most of them are also multi-component, and it is important to make progress in investigating what each component contributes to the intervention.

**Methods:**

The current study will be a three-armed, simple-blinded, randomized controlled clinical trial with a dismantling design. 192 participants will be randomly assigned to: a) an Internet-based Global Protocol condition, which includes traditional therapeutic components of evidence-based treatments for depression (Motivation for change, Psychoeducation, Cognitive Therapy, Behavioral Activation (BA), Relapse Prevention) and PPs component, offering strategies to enhance positive mood and promote psychological strengths; b) an Internet-based BA Protocol condition (without the PPs component), and c) an Internet-based PPs Protocol condition (without the BA component). Primary outcome measures will be the BDI-II and PANAS. Secondary outcomes will include other variables such as depression, anxiety and stress, quality of life, resilience, and wellbeing related measures. Treatment acceptance and usability will also be measured. Participants will be assessed at pre-, post-treatment, 3-, 6- and 12- month follow- ups. The data will be analyzed based on the Intention-to-treat principle. Per protocol analyses will also be performed.

**Discussion:**

To the best of our knowledge, this is the first randomized dismantling intervention study for depression with the aim of exploring the contribution of a PPs component and the BA component in an Internet-based intervention. The three protocols are online interventions, helping to reach many people who need psychological treatments and otherwise would not have access to them.

**Trial registration:**

Clinicalstrials.gov as NCT03159715. Registered 19 May 2017.

## Background

Major depression is projected to become the largest contributor to the disease burden in high income nations by 2030 [1, 2]. Hundreds of controlled and comparative studies have examined the efficacy of psychological treatments for depression [3, 4]. Thus, we have evidence-based interventions for depression, including cognitive behavior therapy (CBT) [5, 6] and behavioral activation (BA) [7, 8], as well as interpersonal [3, 9] or problem-solving therapy [10]. Of all of them, CBT has been extensively researched as an intervention for patients with depression. Studies have shown robust evidence of its efficacy [3, 11–13]. Furthermore, the effect sizes found for CBT have been large compared to waiting list, placebo, or no-treatment conditions [14]. It usually consists of applied cognitive techniques to change thought patterns and behavioral techniques to activate behaviors [13]. However, the efficacy of its therapeutic components is unknown [15]. The literature shows that BA is an essential component of CBT treatments for depression [16–18]. Meta-analyses show that the effects of BA treatment on depressive symptoms are maintained or even improve at 6- and 12-month follow-ups, compared to control conditions and other treatments [7]. Nevertheless, less is known about how depression therapies work and the mechanisms that are responsible for their effects [19, 20]. The US Institute of Medicine indicated that a key step in being able to offer evidence-based interventions in clinical settings is the identification of the core elements of psychological interventions [21]. It has been pointed out that component studies are the best design to examine these core elements [15].

Another important issue related to depression interventions is that, until recently, their therapeutic components focused solely on improving negative symptoms (depressive symptoms, anxiety, etc.), and not on the promotion of positive affect, well-being, and character strengths [22]. Positive psychotherapeutic strategies (PPs) work to help in this issue by promoting positive functioning [22]. The main PPs are Well-being Therapy [23–26], which improves well-being dimensions based on Ryff’s model of eudaimonic well-being [27]; Quality of Life therapy [28, 29], which is more focused on promoting hedonic well-being and life satisfaction in various significant life domains; and Positive Psychotherapy [30, 31], focused on alleviating suffering and systematically enhance happiness by building positive emotions, strengths, and meaning in patients’ lives; and Strengths based Counseling [32, 33]. These interventions have been tested in clinical populations, particularly in depressed patients [34, 35]. They are effective in the improvement of depression and well-being [36, 37]. It has been established in the literature that depressive symptoms are related to lack of meaning in life and low levels of positive emotions, and that depression is more associated with low levels of positive affect than other emotional disorders [38]. Most of the positive interventions promote positive affect, gratitude, resilience, and positive functioning [22], and different studies have pointed out the importance of taking these variables into account as important depression intervention targets [39, 40].

Because depression is a prevalent mental disorder, one of the principal challenges nowadays is to develop new ways to deliver psychological interventions in order to maximize their efficiency and dissemination [41, 42]. Several internationally well-known research groups have launched Internet-based programs in an attempt to address this issue. Results obtained so far show that these online programs are effective in treating depression [3, 43–47]. However, as in the case of face-to-face interventions, most of the Internet-based intervention programs for depression are also multi-component, and it is important to make progress in investigating what each component brings to the intervention.

As mentioned above, component studies are an important tool for examining how therapies work, and they provide an appropriate way to identify the active elements of interventions [48]. With this study design, multicomponent treatments are decomposed, and the complete intervention is compared to an intervention in which a component is eliminated (dismantling studies) or to an intervention with an addition component (additive studies; [49]). There are few studies with a dismantling design in interventions for depression [50]. A recent comprehensive systematic review and meta-analysis of dismantling studies of psychotherapies for adult depression included only 16 studies, none with an Internet-based intervention [15].

Our research group has developed an Internet-based cognitive-behavioral treatment protocol that also includes PPs for patients suffering from depressive symptoms. It has shown its efficacy in different RCTs [51–53]. The results show that this intervention is effective overall, but we do not know the specific contribution of each of its therapeutic components. Using a dismantling strategy could help to identify the contribution of BA and PPs (its main therapeutic components) to the therapeutic change. As a result, this information can contribute to improving intervention programs for depression.

To the best of our knowledge no study with a dismantling design exists with an Internet-based treatment protocol for depression, and even less so with the specific objective of discovering the contribution of BA and PPs.

The objectives of the current study are to (a) evaluate the efficacy at post-treatment and follow-ups (3, 6, and 12 months) of a complete Internet-based protocol for depressive symptoms (including motivation, cognitive restructuring, BA, PPs, Relapse prevention), a protocol for depressive symptoms without PPs, and a protocol for depressive symptoms without a BA component, all of them administered through the Internet to patients with mild to moderate depressive symptoms; (b) analyze the mediators of change in depressive symptoms; and (c) study the acceptability and usability of the intervention.

## Methods/design

### Study design

The current study will be a three-armed, simple-blinded, randomized controlled clinical trial with a dismantling design. Specifically, three groups will be compared: a) an Internet-based Global Protocol condition (IGc), b) an Internet-based BA Protocol condition (IBAc), and c) an Internet-based PPs Protocol condition (IPPc). At this moment, the study is ongoing, and we are in the participant recruitment phase. Participants will be randomly allocated to one of the three experimental conditions.

Randomization will be stratified by levels of depression severity (mild to moderate).

We will carry out block randomization within each stratum to certify that all levels of depression are balanced across the three experimental conditions. The study follows the CONSORT statement (Consolidated Standards of Reporting Trials) [54, 55], CONSORT-EHEALTH [56] and SPIRIT guidelines (Standard Protocol Items: Recommendations for Interventional Trials) [57, 58]. Participants’ assessments will be performed at pre-treatment and post-treatment. Furthermore, there will be three follow-ups: at 3, 6, and 12 months. Figure 1 shows the study flowchart.

**Fig. 1 Fig1:**
[figure not shown]
Study design

### Participants, recruitment and eligibility criteria

The RCT will be carried out at the Emotional Disorder Clinic in Universitat Jaume I. Participants will be adult volunteers with mild to moderate depressive symptoms (from 14 to 28 on the Beck Depression Inventory-II, BDI-II) [59].

Participants will be recruited through the website specially developed for this aim, emails, phone calls, or personal visits, and they will be attended to by a clinician. Once a potential participant has been identified by the clinical psychologist, s/he will be informed about all the characteristics of the study. Any questions or doubts will be clarified in order to ensure that participants have understood all the information correctly. Those who are interested in participating will sign the informed consent. Furthermore, an independent researcher will assess whether they meet all the inclusion criteria.

To participate in the study, participants must meet these inclusion and exclusion criteria. The inclusion criteria are: a) 18 to 65 years old; b) able to read and understand Spanish; c) access to Internet; d) knowing how to use the Internet; and e) experiencing mild to moderate depressive symptoms (from 14 to 28 on the Beck Depression Inventory-II [BDI-II]). Exclusion criteria include: a) receiving a psychological intervention; b) suffering from a severe Axis I mental disorder: alcohol and/or substance dependence disorder, bipolar disorder, psychotic disorder, or dementia; c) having ideation or a significant plan for suicide (assessed by the MINI and item 9 of the BDI-II). Receiving pharmacological medication while participating in the study is not an exclusion criterion. However if the patient has an increase in the pharmacological treatment, s/he will be excluded from the study analysis. Nevertheless, a reduction in the medication does not imply exclusion from the study. We will offer alternative treatments to the participants who do not meet the criteria for the present study.

If the participants fulfill the eligibility criteria, they will be randomized to one of the three experimental conditions by an independent investigator who will not have information about the RCT’s characteristics. Randomization will be performed using a weighted random number sequence generated by a computer, in order to have a homogeneous distribution across the three conditions. The study researchers will be informed about the allocation schedule via telephone call. Before the allocation to one of the three interventions, the patients will agree to participate without having the information about which intervention they will be receive. Nevertheless, for pragmatic reasons, researchers and patients will not be blind to the intervention conditions. At any time during the study, the participants will be allowed to drop out of the intervention without giving any reasons.

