**Sample size and power calculations**

The a priori sample size determination was performed based on the main objective of this investigation. Following Cohen’s (1988) guidelines, we assumed a proportion of explained variance of low magnitude for the interaction between the type of intervention and the measurement occasion, that is, 0.01. For a significance level of 5%, statistical power of 80%, assumed sphericity, and correlation of .7 between repeated measures (following Rosenthal’s 1991 recommendation), the total sample size needed was 147 participants (49 per intervention group). To this figure, an additional 30% was added to anticipate potential dropouts. Therefore, the total sample size of the study was 192 participants (64 per intervention group). Sample size calculations were carried out with the statistical program G*Power 3.1.9.2 [82].

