### Statistical analysis

Per protocol and Intention-to-treat (ITT) analyses will be performed, following the CONSORT and CONSORT-eHealth recommendations [56, 83]. Between-group differences in baseline clinical and socio-demographic characteristics will be explored using analysis of variance (ANOVA) for continuous data, and chi-square tests (χ2) for categorical variables. Both normality and multinormality assumptions will be assessed by applying the Kolmogorov-Smirnov (K-S) test, skewness and kurtosis indexes, and histogram and Q-Q plots. Levene’s test will be conducted to check homoscedasticity assumptions for equality of variances, and Mauchly’s test to explore sphericity assumptions. Missing data patterns will be assessed, and whether missing data are missing completely at random (MCAR) will be checked with Little’s MCAR test [84]. The ITT principle will be applied for primary and secondary outcomes collected at post-treatment, and at the 3, 6, and 12-month follow-ups. In this regard, the maximum likelihood (ML) method using the Expectation Maximization (EM) algorithm will be used to deal with missing data, due to its flexibility in repeated-measures ANOVAs in handling missing data appropriately (i.e., [85, 86]. Nevertheless, several approaches will also be considered and assessed using sensitivity analyses in order to apply the most robust and adequate method based on both missing data patterns and literature recommendations (i.e., [87, 88]. Repeated analysis of variance (rm-ANOVA) will be performed to explore the main and interaction effects of the treatments on all the primary and secondary outcomes. Significant effects will be followed up by pairwise comparisons, such as the Tukey procedure when the homoscedasticity assumption is met, and the Games-Howell procedure if this assumption is not met. Effect sizes (Cohen’s *d*) and their respective 95% confidence intervals (95% IC) will be calculated and reported for within- and between-group comparisons, according to authors’ recommendations [89–91]. In addition to ITT analyses, per protocol analyses will also be conducted. It is true that these analyses suffer from selection bias, but they will allow us to reach conclusions about the efficacy of the treatment in patients who complete all the intervention modules [92].

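### Excluding participants from the analysis when their medication increases contradicts the declared intention-to-treat analysis

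*Protocol article*

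**What the plan says.** The section on participants, recruitment and eligibility criteria permits medication during the trial: "Receiving pharmacological medication while participating in the study is not an exclusion criterion". It then adds: "However if the patient has an increase in the pharmacological treatment, s/he will be excluded from the study analysis". The opposite change is treated differently: "Nevertheless, a reduction in the medication does not imply exclusion from the study".

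The abstract states: "The data will be analyzed based on the Intention-to-treat principle". The Statistical analysis section gives the scope: "The ITT principle will be applied for primary and secondary outcomes collected at post-treatment, and at the 3, 6, and 12-month follow-ups". It also announces a per-protocol analysis, whose purpose is to describe the "efficacy of the treatment in patients who complete all the intervention modules". Medication is not mentioned there.

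**The concern.** An ITT analysis keeps every randomised participant in the arm assigned, whatever happens later. A rule that removes people because of a later event cannot operate inside such an analysis, so an analyst who follows one statement breaks the other. The conflict reaches every primary and secondary comparison at every time point.

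The rule is also one-sided, since an increase removes the participant and a reduction does not. In a depression trial an increase may well follow a poor response. If so, exclusion depends on the outcome, and the arm that fails more people loses more of them and looks better for it. Participants and researchers know the assigned condition, so the frequency of medication changes could itself differ by arm. All three arms are active and share several modules. True differences may therefore be small, and even a modest bias would matter.

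**Working it through.** **1. Can the statements be reconciled?**

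- *As an eligibility rule?* No. The preceding sentence concerns medication during participation, eligibility is settled before randomisation, and the penalty is removal from the analysis. That it acts after randomisation is an inference, but it is the only workable reading.
- *As a per-protocol rule?* No. The sentence names no analysis set, and the article describes the per-protocol population by module completion alone.
- *As a missing-data matter?* No. Maximum likelihood with the EM algorithm is planned for data that are missing. Here the rule itself takes participants out.

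The contradiction therefore stands without any calculation.

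**2. Possible bias (assumed inputs).** The article gives no rate of medication increase and no outcome difference for those affected. Let *p* be the proportion excluded in an arm and Δ the amount, in SD, by which excluded participants are worse than those retained.

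- The full-arm mean is worse than the retained mean by *p* × Δ, so within-arm bias = *p* × Δ.
- Between-arm bias = (*p*₁ − *p*₂) × Δ.
- Equal rates: 0 × Δ = 0.
- Rates of 15% and 5%: 0.10 × 0.5 = 0.05 SD, and 0.10 × 1.0 = 0.10 SD.

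A second model, also assumed, makes the probability of an increase logistic in the outcome score: 5–20% at the better arm's mean, with a log-odds slope of 1 to 2 per SD. A true difference of 0.30 SD then shrinks to between 0.28 and 0.21 SD among those retained. The better arm loses 7–30% and the worse arm 9–38%.

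**3. Power.** The inputs come from the section on sample size and power calculations: explained variance 0.01 for the interaction, α 0.05, correlation 0.7, sphericity, three groups.

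- *f* = √(0.01/0.99) = 0.1005.
- λ = *f*² × N × m/(1 − ρ), with df₁ = (3 − 1)(m − 1) and df₂ = (N − 3)(m − 1).
- The article's figure, with m = 2 occasions and N = 147: λ = 0.0101 × 147 × 2/0.3 = 9.90, power 0.803. The stated 147 is reproduced.
- 49 × 1.3 = 63.7, rounded up to 64 per group, gives 192. The 30% is for dropouts, and nothing is added for medication exclusions.

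Power with m = 2:

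| Situation | N | Power |
|---|---|---|
| All 192 analysed | 192 | 0.90 |
| 30% dropouts lost (192 × 0.7) | 134 | 0.76 |
| and a further 5% excluded | 128 | 0.74 |
| and a further 10% excluded | 121 | 0.71 |
| and a further 20% excluded | 108 | 0.66 |

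The part due to the medication rule is 0.763 − 0.739 = 0.024 at 5% and 0.763 − 0.658 = 0.105 at 20%, or about 2 to 10 points. If dropouts are instead kept through the missing-data method, excluding 5–20% of 192 leaves about 182 to 154, with nominal power 0.89 to 0.82.

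**The case against.** The best defence is that a dismantling trial wants the effect of its components free of added drug treatment, so setting aside participants whose medication rises answers a legitimate question. That justifies a secondary analysis. It does not make the exclusion compatible with ITT, and the article does not describe its main analysis as a modified ITT. Its closing remark that statistical procedures may vary does not resolve the conflict either.

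Several stronger readings are tempting but not supported:

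- *Poor responders are certainly removed and every arm's improvement is inflated.* The article gives no reason for increases and speaks of pharmacological treatment in general. Increases for unrelated conditions would cost participants without selecting on outcome. Nor does it say that a reduction means the participant is doing well.
- *The rule acts over 16 weeks of treatment plus 12 months of follow-up.* The article ties it to participation and gives no end date, so this window is an inference.
- *The bias is a fixed share of the difference the trial is sized for.* Only the explained variance of 0.01 is stated. With two occasions it corresponds to a difference in change of *f* × √18 = 0.43 SD if one arm differs from two equal arms, but *f* × √24 = 0.49 SD if the arms are evenly spaced.
- *The rule brings power down to 74–66%.* Most of the fall from the 0.90 available with all 192 comes from assuming that 30% dropouts are lost, which alone gives 0.76.

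These points limit what can be said about direction and size. They leave the contradiction untouched.

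**Conclusion.** The point holds as a contradiction within the article. An unrestricted exclusion triggered by an event after randomisation cannot coexist with an ITT analysis of all primary and secondary outcomes. This should be corrected before analysis, because it decides who is counted in every main comparison.

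The consequences are conditional. If increases follow worsening depression, within-arm improvement is overstated and the arm with more increases is favoured. With an assumed deficit of 0.5–1.0 SD, the between-arm bias runs from 0 at equal exclusion rates to 0.05–0.10 SD at rates 10 percentage points apart. The loss of power due to the rule is about 2 to 10 points for exclusions of 5–20%, provided dropouts are lost as well. It is secondary to the conflict over the analysis set.

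**What to change.** Reconcile the eligibility section with the abstract and the Statistical analysis section by replacing the exclusion sentence with text to this effect:

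*Participants whose pharmacological treatment increases after randomisation remain in the ITT analysis with all their data and continue the scheduled assessments. Any increase is recorded with its date. These participants are excluded only from the per-protocol set and from one sensitivity analysis. The number and timing of increases are reported by arm.*

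The per-protocol description in the Statistical analysis section should then mention medication increases alongside module completion.

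The cost is a few sentences and one small data item. Table 4 lists no medication measure, so dated increases would have to be added to what is collected. Continued assessment must be stated, because the article does not say whether follow-up goes on after an increase. The article reports that recruitment is still under way, so the change can be made before analysis. It concerns the analysis set only and leaves medication management as it is.

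### Allocation concealment from recruiting and screening staff is not secured as written: the study researchers are told the schedule, with no timing set and only patients kept unaware

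*Protocol article*

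**What the plan says.** All but two of the relevant statements are in the protocol article under Participants, recruitment and eligibility criteria.

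- **Who randomizes, and when.** Once eligibility is met, participants follow this route: "they will be randomized to one of the three experimental conditions by an independent investigator who will not have information about the RCT’s characteristics".
- **What is passed on.** "The study researchers will be informed about the allocation schedule via telephone call".
- **Who is kept unaware beforehand.** Before allocation, "the patients will agree to participate without having the information about which intervention they will be receive". No matching sentence covers staff.
- **Blinding during the trial.** For pragmatic reasons, "researchers and patients will not be blind to the intervention conditions". Study design labels the trial simple-blinded without saying who is blinded.
- **How the sequence is built.** Study design says: "We will carry out block randomization within each stratum", the strata being levels of depression severity. The participants section says: "Randomization will be performed using a weighted random number sequence generated by a computer", and does not mention blocks. No block size is given.
- **Who meets candidates.** "Once a potential participant has been identified by the clinical psychologist, s/he will be informed about all the characteristics of the study". Signed consent follows.
- **Who decides eligibility.** The participants section gives this to an independent researcher. The Support section gives the diagnostic interview and the check of the inclusion criteria to a predoctoral student in the research group, who also makes the later support calls.

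**The concern.** An allocation schedule is ordinarily the list of assignments, not one person's arm. Concealment exists to keep that list from anyone who can influence whether or when a candidate enters. Here the sentence names the study researchers as recipients and the schedule as what they receive, and it sets no condition on timing.

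If staff in contact with candidates know the next arm, they can encourage, discourage or delay entry. The three groups may then differ at entry in ways that stratifying by severity does not remove. A dismantling trial depends on such between-arm contrasts, and this one is planned around a small interaction (explained variance 0.01). Analysis cannot reliably undo selective entry, because the reasons for it are not recorded.

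**Working it through.** The plan gives no figure on concealment, so there is none to reproduce. The check is mainly a comparison of statements, followed by a short illustration.

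**1. Order of events.** The participants section runs: candidate identified and informed, consent signed, inclusion criteria assessed, randomization by an independent investigator. Up to that step, the order protects concealment. The telephone sentence follows with no time attached. It could mean one call per participant after randomization, or a call that conveys the list. The text does not exclude the second.

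**2. Who is covered.** The statement about not knowing the upcoming arm applies to patients. The non-blinding sentence concerns knowledge of the condition during the trial; it is not itself a statement about future assignments. It does mean that past assignments are visible to the team.

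**3. Who screens.** If an outsider screens, a call to the study team matters less for the eligibility decision. If the predoctoral student screens, a member of the group decides entry. The two sections disagree, and neither says whether the person telephoned is the person who screens. In either case the clinical psychologist meets candidates before consent.

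**4. Illustration of predictability.**

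Inputs: three arms and 192 participants (from the article). Block size *b* is assumed, because the article gives none. It is also assumed that blocks are fixed, complete, of known size and equally allocated, with *r* = *b*/3 places per arm.

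*Whole list disclosed:* 100% of next assignments are known, against 1/3 by chance.

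*Only past assignments known:* an assignment is certain when all remaining places in the block belong to one arm. The expected number certain per block is

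1 + (r−1)/(b−1) + [(r−1)(r−2)]/[(b−1)(b−2)] + …

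- b = 3: 1; 1/3 = 33.3%; 192 × 0.333 = 64 participants
- b = 6: 1 + 1/5 = 1.2; 1.2/6 = 20.0%; about 38
- b = 9: 1 + 2/8 + (2/8)(1/7) = 1.286; 1.286/9 = 14.3%; about 27
- b = 12: 1 + 3/11 + (3/11)(2/10) + (3/11)(2/10)(1/9) = 1.333; 1.333/12 = 11.1%; about 21

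The best-guess success rate for b = 3 is (1/3 + 1/2 + 1)/3 = 61%. Exact enumeration gives 56%, 53% and 51% for b = 6, 9 and 12.

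These figures describe what could be foreseen. They do not say that anyone acted on it.

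**The case against.** The strongest reply is that the sequence of steps already conceals. Eligibility is settled, an outsider randomizes, and then a call is made. On that reading the call reports the arm of someone already accepted. An independent randomizer would serve little purpose if the list were handed over, and a telephone call is an odd way to pass on 192 assignments. The English is loose elsewhere, so schedule may simply mean allocation. This reading is plausible, and it rules out treating advance knowledge as established.

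Three stronger inferences are tempting, and the documents do not support them.

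- *That the researchers who receive the schedule also screen and enrol.* The Support section shows a group member screening, but the participants section names an independent researcher, and neither identifies the person telephoned.
- *That the plan should be faulted for not fixing varying, undisclosed block sizes.* A condensed article may leave block size to the full protocol. The predictability figures need a fixed and known size, which the article does not state.
- *That the false-positive rate rises by a calculable amount.* This would need an assumed steering bias that nothing in the article supplies, so no such figure is offered here.

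What the reply does not answer is that the sentence names the schedule, gives no timing, and has no counterpart for staff to the assurance given about patients. The article addresses this step explicitly and words it in a way that permits disclosure; this is not merely a detail left out.

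**Conclusion.** The point holds in a limited form. As written, concealment of upcoming assignments from recruiting and screening staff is not secured, and the two accounts of who decides eligibility conflict. The article does not show that the list was shared, that the person telephoned screens candidates, or that the arms are unbalanced.

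The possible exposure runs from none (single arms released after entry is final, blocks not inferable), through 11.1% to 33.3% of assignments foreseeable (single arms, assumed fixed and known blocks of 12 down to 3), to all of them (list disclosed). Which case applies depends on what the telephone sentence means in practice. Correction is worthwhile because it costs almost nothing and, at the time of writing, recruitment was still under way. Confidence is moderate, since the ambiguity rests largely on one word.

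**What to change.** Replace the telephone sentence with wording such as: *The independent investigator alone holds the randomization sequence. For each participant, once signed consent, confirmed eligibility and the severity stratum have been recorded as final, the investigator telephones that participant's arm only. The sequence is not disclosed to study researchers.*

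Reconcile the participants and Support sections on who administers the diagnostic interview and who decides eligibility, and state whether that person learns allocations.

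If the list has in fact been shared, generate a new sequence for the unused part and report the date of the change.

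The cost is a change of wording, using the independent investigator and telephone route already in place. The sample size of 192 and the analysis are unaffected. A new list is needed only if disclosure occurred, and it protects only participants not yet randomized.
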